#### Control participants

Participants in the control group will receive an upper body strength and fitness program provided three times per week for 12 weeks. This program may be provided at the spinal unit or an appropriately equipped gymnasium as approved by the Project Committee. The program will be a circuit-based exercise program incorporating resistance and cardiorespiratory training. For this protocol, the circuit will comprise several stations using different pieces of equipment and with minimal time to rotate between stations. The participants will be supervised by a therapist and/or clinical exercise instructor, and exercises will be progressed as appropriate to build strength and endurance in the intensity range of 6–20 repetition maximum (RM). Exercises could include hand cycling, chest press, boxing, lateral pull-downs and rowing. Guidelines for the content and delivery of exercises will be clearly outlined in a handbook to ensure standardization across sites.

#### Wash-out and follow-up period

For 3 weeks prior to the intervention, participants will cease any formal intensive exercise programs in which they are participating. During the program, participants will not undertake any formal intensive exercise programs in addition to those provided in the study protocol. At the end of the 12-week intervention period, there will be no restriction placed on participants with respect to undertaking further exercise.

#### Quality assurance

To ensure that treatments are of a high standard and delivered in accordance with the trial protocol, therapists responsible for the administration of the exercise programs will attend workshops where they will be trained in the delivery of the treatment program and in assessment procedures. The workshops will cover locomotor training (4 days), FES-assisted cycling training (2 days), trunk training (2 days), upper body training (1 day) and assessment procedures (1 day). Therapists will also be provided with a written protocol, and standardized case report forms for documentation of assessments and interventions provided.

### Outcome assessments

Assessments will occur at baseline, 12 weeks after the commencement of the intervention, and then at 6 months and 12 months after randomization. All assessments will be undertaken by therapists blinded to group allocation. Any inadvertent unblinding of assessors will be reported. In addition, the success of blinding will be estimated by asking assessors to guess the participant’s group allocation at the completion of each post-randomization assessment.

### Primary outcome

#### The primary outcome measure is the American Spinal Injuries Association (ASIA) motor score at 12 weeks

The ASIA Motor Score is derived from part of the assessment for the International Standards for Neurological Classification of Spinal Cord Injury [19]. It involves testing the strength of ten key muscles on each side of the body in the supine position (e.g., elbow flexors, wrist extensors, hip flexors, quadriceps, dorsiflexors) on a scale of 0 = no contraction to 5 = normal resistance through full range of motion. Scores are summed to give a total possible score of 50 for the upper extremities and 50 for the lower extremities.

### Secondary outcome measures are

#### ASIA motor and sensory scores at 6 months and 12 months

The ASIA Motor Assessment will be undertaken as described above. The ASIA Sensory assessment is also part of the assessment for the International Standard for Neurological Classification of Spinal Cord Injury. It involves testing pinprick and light touch sensation at key points representing each dermatome. Pin-prick and light-touch sensation of each dermatome is separately scored on a 3-point scale (0, 1 and 2). Scores will be summed to give a total possible score of 224 where a higher score indicates better sensation than a lower score.

#### Leg exercise capacity test at 12 weeks, 6 months and 12 months

Participants will perform a graded exercise test using their legs (FES cycling), following the protocol of Heesterbeek et al. [25]. The electrical stimulation current amplitude will be increased manually from the lowest current amplitude that evokes minimum muscle contraction up to 100% amplitude of the cycle’s stimulator output (~140 mA). The timing of FES stimulation current amplitude increments will be based on the prevailing heart rate response between resting heart and age-predicted maximum heart rate. The measures of interest will be change of peak power output (W), peak heart rate (b•min^-1^) and change of sub-maximal heart rate (b•min^-1^) during the 20 W and 40 W stages and during the incremental portion of the leg cycling.

#### Spinal cord independence measure (SCIM) at 12 weeks, 6 months and 12 months

The SCIM was designed specifically for patients with spinal cord injuries. It focuses on the spinal cord injured person’s ability to perform basic everyday tasks and takes into consideration the economic burden of disability as well as the impact of disability on the participant’s overall medical condition and comfort [26,27]. The SCIM consists of three complementary subscales: ‘Self care,’ ‘Respiration and sphincter management’ and ‘Mobility’.

#### Anthropometry at 12 weeks, 6 months and 12 months

Body mass index (BMI) will be estimated from body mass and lying stature. Skin fold calipers will be used to assess change in body adiposity at 12 sites on the body while the participant is lying horizontal [28]. Abdominal circumference, chest circumference and leg circumferences will be assessed at the greatest girth-points.

#### Measures of trunk function at 12 weeks, 6 months and 12 months

*Maximal balance range*[29] will be measured by asking participants to reach as far forward as they can without falling and then return to their starting position. The distance reached will be measured using a sway meter, a 40-cm hinged rod fastened by a firm belt to the participants’ chest at the level of the axilla and extending in a horizontal plane from the body. A ballpoint pen mounted at the end of the rod will record the movements of the upper body on a sheet of graph paper fixed to the top of a height-adjustable table with a meter-long ruler taped to the side. The resultant trace will be measured in terms of the maximal anteroposterior (AP) displacement in centimeters traversed by the pen. The participants will have two attempts at the test, with the longer distance (maximal AP distance moved) taken as the test result. A long distance is considered a better performance. This score will be corrected for body height (score × mean height/participants’ height) measured from the center of the sway meter strap to the top of the seat.

*The Spinal Cord Injury-Falls Concern Scale (SCI-FCS)*[30] is a questionnaire adapted from the Falls Efficacy Scale-International [31] and worded appropriately for activities undertaken by people in wheelchairs. Participants will be asked to record on a 4-point scale how concerned they are about falling when performing each activity. A score of 1 reflects ‘not at all concerned’ and a score of 4 reflects ‘very concerned.’ Scores on each item will be summed.

#### Spasticity at 12 weeks, 6 months and 12 months

Spasticity over the previous week will be measured via self-report using the Penn Spasm Frequency Score (PSFS) [32,33]:

0 = No spasms

1 = Spasms induced by stimulation

2 = Spasms occurring less than once per hour

3 = Spasms occurring more than once per hour

4 = Spasms occurring more than 10 times per hour

Any change in the dosage of anti-spasticity medication during the intervention period will also be monitored.

#### Multidimensional pain inventory (spinal cord injury version) at 12 weeks, 6 months and 12 months

Pain will be measured using the spinal cord injury version of the Multidimensional Pain Inventory (SCI-MPI) [34,35]. This is a comprehensive instrument designed to assess a range of self-reported behavioral and psychosocial factors associated with chronic pain syndromes and has been validated in the spinal cord injury population.

#### Walking tests at 12 weeks, 6 months and 12 months

Walking tests will be conducted only in participants capable of ambulation. The 6-Minute Walk Test (6MWT) is a self-paced task that measures the distance that a participant can walk in 6 min. The participant may stop to rest at any point. The test may be performed either indoors or outdoors, along a long, flat, straight and hard surface, preferably 30 m in length, marked every 3 m, with a turnaround point marked with a cone. The distance (total distance walked rounded to the nearest meter) will be measured. The fatigue level will also be reported.

The 10 Meter Walk Test (10MWT) measures the time required to walk 10 m. Participants will walk at their preferred walking speed. They may use an assistive device and must wear shoes. To minimize the effects of acceleration and deceleration, participants will commence walking at least 2 m before the start of the 10 m walking track and continue for 2 m beyond the end of the track (14 m altogether). The time (seconds) will be measured over the intermediate 10 m and walking speed calculated in m•s^-1^.

#### Psychological measures at 12 weeks, 6 months and 12 months

Stress will be measured using the Perceived Stress Scale (PSS) [36], which is the most widely used psychological instrument for measuring the perception of stress. Depression will be measured using the Hospital Anxiety and Depression Scale (HADS) [37]. Physical Self-Concept will be measured using the Multidimensional Health Locus of Control [38]. Self-Efficacy will be measured using the Moorong Self-Efficacy Scale [39,40] and Self Esteem using the Rosenberg Self-Esteem Scale [41]. All of these tools have previously been used in people with spinal cord injury.

#### Quality of life at 12 weeks, 6 months and 12 months

The Health Utilities Index Mark 3 (HUI3) is a measure of health-related quality of life widely used around the world in population health surveys, clinical studies and cost-utility analyses. HUI3 includes eight attributes (vision, hearing, speech, ambulation, dexterity, emotion, cognition and pain), with five or six levels for each attribute. The HUI3 is able to discriminate various aspects of burden associated with chronic conditions as well as describing the differences in overall health-related quality of life levels [42]. In addition, the Assessment of Quality of Life (AQoL)-8, which is a self-administered 8-item questionnaire [43], is also used for two reasons. One is that this instrument was developed relatively more recently based on the utility value of Australian population. The other is to provide an alternative source of information from a different instrument.

The WHOQoL-Bref questionnaire was designed by an international collaboration on quality of life by the World Health Organization. It contains 26 questions about many different aspects of quality of life, with some additional questions about the person and his/her health. It has been found to be a valid measure in people with spinal cord injury [44].

### Economic outcomes

Economic evaluation will determine whether the experimental intervention is cost-effective compared to the control intervention. The incremental cost-effectiveness analysis will measure incremental costs in the two groups in relation to the AIS Motor score, divided by the incremental change in health utility and quality of life measures. This study employs a societal perspective. Therefore, all relevant costs associated with participants and delivery of experimental and control interventions will be included. The cost of treatment will be estimated using standard costs for therapy and actual costs of training equipment expressed as a mean cost of treatment per participant. Community-based resource use from the time of randomization will include data on visits to GPs, specialists or other health care providers, pharmaceutical costs, as well as data on resource use specifically relating to levels of independent functioning (aids, equipment, community services, e.g., home help, home maintenance, meals on wheels, transport, formal and informal care, cost of home modifications, etc.). The potential loss of productivity of the participant will also be measured.

Treatment effectiveness will be determined by the primary endpoint, as well as the health utility and quality of life measures. Cost-effectiveness will be calculated as the cost per patient treated. These calculations will be based on the number of participants effectively treated in the intervention group minus the number of participants who also meet the criteria of ‘effectively treated’ in the control group. Lifetime cost and effectiveness will be modeled using decision-tree and Markov processes.

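### The incremental cost-effectiveness ratio puts motor score and utility into one quotient, and the responder measure beside it is mislabelled and uses numbers instead of proportions

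*Protocol article*

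**What the plan says.** The section Economic outcomes of the protocol article sets out two cost-effectiveness measures.

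The first is the incremental analysis: "The incremental cost-effectiveness analysis will measure incremental costs in the two groups in relation to the AIS Motor score, divided by the incremental change". The divisor in full reads: "divided by the incremental change in health utility and quality of life measures".

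The second comes in the next paragraph. It opens with the effectiveness measures: "Treatment effectiveness will be determined by the primary endpoint, as well as the health utility and quality of life measures". It continues: "Cost-effectiveness will be calculated as the cost per patient treated". The sentence after that supplies an effect: "These calculations will be based on the number of participants effectively treated in the intervention group minus the number of participants who also meet" the same criteria in the control group.

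The cost of treatment is to be "expressed as a mean cost of treatment per participant". The section also takes a societal perspective and plans lifetime modelling with decision trees and Markov processes. The Abstract lists cost effectiveness among the secondary outcomes.

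**The concern.** An incremental cost-effectiveness ratio has one cost difference above the line and one effect difference below it. Only then can the result be read as the price of a unit of effect. The first measure has two effects in the same expression: the motor score, to which costs are related, and the utility and quality-of-life change, by which the result is divided. Its unit would be money per motor point per utility unit. No willingness-to-pay threshold exists on that scale, and the figure cannot be compared with a cost per QALY from elsewhere.

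The divisor is also plural. The section Quality of life names HUI3, AQoL-8 and WHOQoL-Bref, which are different instruments on different scales, so no single divisor is identified.

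The second measure carries a label that contains no effect, and its effect is a difference in numbers of participants while treatment cost is a mean per participant. An analyst who takes the label or the units at face value would report a different quantity from the one intended.

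**Working it through.** The section gives no numerical result, so there is none to reproduce. The check compares the definitions as written with the usual forms. Planned arm sizes come from the article. Costs, utility gains and response rates are not in the article and are assumed here for illustration only.

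**Inputs from the article.** Allocation is 1:1 (Randomization). Sample size: 150 / 0.8 = 187.5, rounded up to 188, so 94 per arm. The planning difference in motor score is 4.0. Primary and secondary endpoints are analysed on all randomized participants, with multiple imputation (Statistical analysis).

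**Assumed.** Difference in mean cost ΔC = 10,000 (15,000 v 5,000). Motor difference ΔM = 4. Utility difference ΔU = 0.05. Response 30% v 20%.

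**1. The first measure.** The usual ratios are

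- ΔC / ΔM = 10,000 / 4 = 2,500 per motor point
- ΔC / ΔU = 10,000 / 0.05 = 200,000 per utility unit

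The sentence as written gives (ΔC / ΔM) / ΔU = 2,500 / 0.05 = 50,000, which is neither. Varying the effects with ΔC held at 10,000:

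| ΔM | ΔU | ΔC / ΔU | Quotient as written |
|---|---|---|---|
| 2 | 0.05 | 200,000 | 100,000 |
| 4 | 0.05 | 200,000 | 50,000 |
| 8 | 0.05 | 200,000 | 25,000 |
| −4 | −0.05 | −200,000 | 50,000 |

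In the first three rows the cost of a utility unit does not move, yet the quotient changes fourfold. In the last row the programme costs more and does worse on both effects. The separate ratios turn negative (−2,500 and −200,000), which shows that it is dominated. The quotient is the same as in the second row, where both effects are gains.

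**2. The label of the second measure.** Taken alone, cost per patient treated is 15,000 in the experimental arm whatever the effect. Taken with the following sentence, the measure is cost per additional participant effectively treated: 10,000 / (0.30 − 0.20) = 100,000. It does respond to the effect: at 50% v 20% it is 10,000 / 0.30 = 33,333.

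**3. Numbers against proportions.** With 94 per arm, the difference in numbers is 0.30 × 94 − 0.20 × 94 = 28.2 − 18.8 = 9.4.

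- Total cost difference over difference in numbers: (10,000 × 94) / 9.4 = 100,000, as it should be.
- Mean cost difference over difference in numbers: 10,000 / 9.4 ≈ 1,064, too small by a factor of 94.

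The mismatch of units is therefore present even with equal arms, if the stated mean cost is put over the stated count.

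**4. Arm size.** At 94 v 94 the difference in numbers is exactly 94 times the difference in proportions, so there is no distortion from arm size. With an assumed 98 v 90:

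- 30% v 20%: 29.4 − 18.0 = 11.4, against 9.4 with equal arms.
- 30% in both arms: 29.4 − 27.0 = 2.4, where the true difference is 0.

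**The case against.** The strongest defence is that the first sentence is loosely worded and means two analyses: cost against motor score, and cost against utility and quality of life. The later sentence naming both kinds of effectiveness measure fits that reading, and a condensed article leaves detail to a fuller document. The reading is plausible. But the article gives an operation, a division, and on its wording both effects enter one expression. If two ratios are meant, the text has to say so.

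On the second measure the defence largely succeeds. A reader might infer that it contains no effect at all. The document does not support this: the next sentence ties the calculation to the difference in participants effectively treated, so the fault is in the label.

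A reader might also infer that counting participants seriously biases the result through unequal dropout. The design does not support that either. Allocation is 1:1, and secondary endpoints are analysed on all randomized participants with imputation, so the analysed arms should be close to equal. What remains is the mismatch between a count and a mean cost per participant.

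The article gives no cut-off for being effectively treated. It refers to criteria, and their definition may stand in the full protocol or analysis plan, so this is not counted as a fault.

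**Conclusion.** The point holds for the first measure. Followed literally, the incremental ratio mixes two effects, depends on the motor effect when cost per utility unit is fixed, and cannot tell two gains from two losses. It cannot show whether the programme is cost-effective. The second measure is a sound idea under the wrong label, with a count where a proportion is needed.

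It would go too far to say that the economic question cannot be answered at all. The second measure, read whole, is an ordinary incremental comparison with control, and lifetime modelling is planned as well.

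The defect is confined to the secondary economic evaluation. It does not touch the primary ANCOVA, the allocation or the sample size. The amounts shown rest on assumed costs and effects. They show how the formulas behave and do not predict the error in any trial result. The factor of 94 applies only if a mean cost is divided by a count at the planned arm size.

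**What to change.** Replace the incremental-ratio sentence with two separate ratios:

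- (a) difference in mean societal cost divided by difference in mean QALYs (or utility), from the utility instruments already collected, with each instrument reported separately;
- (b) difference in mean cost divided by the baseline-adjusted difference in ASIA Motor Score.

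Rename the second measure cost per additional participant effectively treated. Define it as the difference in mean cost per participant divided by the difference in proportions effectively treated. Both parts are then on a per-participant basis, and the result does not depend on arm size. The measure need not be dropped.

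The cost is a few sentences. The Abstract says that all outcomes are measured at baseline, 12 weeks, 6 months and 12 months, and resource use is already recorded from randomization, so no new data are needed. The wording should be settled before costs and outcomes are compared by arm, so that the choice of ratio does not follow the results.

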### Statistical analyses

#### Sample size

This power analysis is for a one-way fixed effects analysis of covariance with two levels that correspond to experimental and control arms of the study. This analysis includes baseline value of AIS Motor Score as a covariate and uses week 12 values as the primary outcome. Available pilot data [9] demonstrate a mean change in the AIS Motor Score of 4.8 (SD = 1.0) in an intensive exercise group compared to a mean change of 0.1 (SD = 0.5) points in the control group from the comparable baseline of 40. Assuming the more conservative difference in mean changes in AIS Motor Score between the groups of 4.0, a similar baseline mean AIS Motor score of 40 and a correlation between the baseline and week 12 ASIA Motor score of 0.8, the resulting analysis of covariance effect size (f) is 0.22. The corresponding total sample size of 150 participants equally distributed between experimental and control arms will yield power of 0.8 to reject the null hypothesis at a 0.05 level of significance. The analysis of variance is non-directional (i.e., two-tailed), which means that an effect in either direction will be interpreted. Allowing for 20% dropout rate, the final sample size for this study is calculated to be 188 patients equally distributed between experimental and control arms.

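### The effect size f = 0.22 cannot be derived from the inputs printed with it, the quoted pilot SDs do not explain it, and at N = 150 it gives about 76% power, not 80%

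*Protocol article*

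**What the plan says.** All the relevant text is in the protocol article, under Statistical analyses, Sample size.

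- **Model.** A two-arm analysis of covariance: "This analysis includes baseline value of AIS Motor Score as a covariate and uses week 12 values as the primary outcome".
- **Pilot data.** "a mean change in the AIS Motor Score of 4.8 (SD = 1.0) in an intensive exercise group", set against "a mean change of 0.1 (SD = 0.5) points in the control group from the comparable baseline of 40".
- **Planning difference.** "Assuming the more conservative difference in mean changes in AIS Motor Score between the groups of 4.0", with a baseline mean again taken as 40.
- **Correlation and effect size.** "a correlation between the baseline and week 12 ASIA Motor score of 0.8, the resulting analysis of covariance effect size (f) is 0.22".
- **Size.** "The corresponding total sample size of 150 participants equally distributed between experimental and control arms" is said to give power of 0.8 at the 0.05 level, two-tailed. A 20% dropout allowance raises 150 to 188.

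The only SDs in this derivation are the two pilot SDs of change. No SD of the motor score at baseline or at week 12 appears in it.

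**The concern.** The section reads as a complete derivation, running from pilot means and SDs through difference, correlation and f to N, power and dropout. A reader should be able to retrace it, and cannot. The quantity that links a 4.0-point difference to f is the SD of the score, which is absent, while the baseline mean, which is listed, does not enter f.

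The variability that is shown points to a quite different effect size. This matters because the unstated SD determines the size of the trial, and N is sensitive to it. With a 4.0-point difference and correlation 0.8, 80% power needs 104 participants if the score SD is 12, 162 if it is 15 and 286 if it is 20. Without the planning SD, nobody can judge whether it suits a population with complete and incomplete injuries from C6 to T12 scored from 0 to 100, or say later whether a null result reflects no effect or more variability than planned.

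**Working it through.** **Inputs** (all from the Sample size section): difference 4.0; correlation 0.8; f = 0.22; N = 150 in two equal arms; two-sided alpha 0.05; power 0.80; pilot SDs of change 1.0 and 0.5. The score SD is assumed equal at the two visits.

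**Formulas for two equal arms**

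- f = (difference / 2) / adjusted SD
- adjusted SD = score SD × sqrt(1 − 0.8²) = 0.6 × score SD
- change SD = score SD × sqrt(2 × (1 − 0.8)) = 0.632 × score SD
- power from the noncentral F distribution with 1 and N − 3 degrees of freedom and noncentrality N × f²

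**1. Reproducing f.** This is not possible. Without a score SD the formula has an unknown, and the mean of 40 does not supply it.

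**2. Working back from f = 0.22**

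- adjusted SD = 2.0 / 0.22 = 9.09
- score SD = 9.09 / 0.6 = 15.15 (14.8 to 15.5 if f was rounded from anywhere between 0.225 and 0.215)
- change SD = 15.15 × 0.632 = 9.58

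Comparing change SD with change SD: 9.58 / 1.0 = 9.6 and 9.58 / 0.5 = 19.2. The score SD of 15 is on another scale and should not be set directly against 1.0 and 0.5.

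**3. Working forward from the pilot SDs, pairing them with the planning correlation of 0.8**

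| Change SD | Score SD | Adjusted SD | f |
|---|---|---|---|
| 1.0 | 1.58 | 0.95 | 2.11 |
| 0.5 | 0.79 | 0.47 | 4.22 |

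Either value of f is about 10 to 19 times the stated 0.22, and a handful of participants would then suffice.

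**4. Could 0.22 be an effect size without baseline adjustment?** The SD would then be 2.0 / 0.22 = 9.1, still 9 and 18 times the pilot SDs.

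**5. N and power at the stated f**

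- f = 0.22, N = 150: power 76.3% (76.9% by normal approximation)
- N for 80% power: 166 (164 by normal approximation)
- f = 0.225, the largest value that could round to 0.22: N = 158, so rounding does not account for 150
- f giving 80% power at N = 150: about 0.230, a score SD of about 14.5
- detectable difference at N = 150, 80% power and adjusted SD 9.09: 2 × 0.230 × 9.09 ≈ 4.2 points
- dropout step: 150 / 0.8 = 187.5, rounded up to 188, which does reproduce

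**6. Sensitivity at N = 150, difference 4.0** (SD and correlation are assumptions, not figures from the article)

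| Score SD | Correlation | Power |
|---|---|---|
| 12 | 0.8 | 92% |
| 15 | 0.8 | 77% |
| 20 | 0.8 | 53% |
| 20 | 0.7 | 40% |
| 20 | 0.9 | 80% |

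**The case against.** The strongest reply is that the article never says f was calculated from the pilot SDs. It cites the pilot for the size of the change, then opens a new sentence with its own planning assumptions. The Background section describes that study as non-randomized, with groups differing in time since injury, so declining to adopt its variability would be reasonable. The correlation of 0.8 is also the trial's assumption and not a pilot result, so the forward values of f depend on pairing figures from two sources. With a score SD of 15.15, a change SD of 1.0 would need a correlation of about 0.998, which is implausible but not impossible.

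This part stands. A reader might infer that the pilot SDs and f cannot both be right, or that the pilot SDs are standard errors under the wrong label. The documents support neither inference: they do not say which SD was used, and the pilot report is not available here. A reader might also infer from the sensitivity table that the trial is badly underpowered. The low values belong to assumed SDs for which the article gives no basis.

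A second reply is that a journal article may leave the planning SD to the full protocol. As a bare omission that would be fair. Here, however, the article prints the whole derivation and says that f results from the listed inputs, which it cannot. The power shortfall needs no unstated SD at all: f, N, alpha and power are all printed and do not agree.

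**Conclusion.** The point holds in this form. The stated f = 0.22 does not follow from the inputs given for it. It implies a score SD of about 15.2 and a change SD of about 9.6 (difference 4.0, correlation 0.8, equal SDs at both visits). The pilot change SDs beside it are smaller by factors of about 10 and 19, so they do not explain f and have to be reconciled with it. Which figure is at fault, if either, cannot be settled from the article.

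Separately, and with no assumption about the SD, f = 0.22 at N = 150 gives about 76% power at two-sided 0.05. That is about 4 percentage points below the stated 80%, or 16 participants short of the 166 needed. The shortfall is modest. The larger weakness is that the SD behind the sample size cannot be checked, while power depends strongly on it.

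**What to change.** 1. Check the two pilot SDs against their source and reconcile them with f, correcting or explaining whichever needs it.
2. State the planning score SD and where it comes from, and show the calculation: f = (4.0/2) / (SD × sqrt(1 − 0.8²)).
3. Restate the power at N = 150 as about 76%, or keep 80% and restate the detectable difference (about 4.2 points at the implied SD). Neither adds patients.
4. Show power over a range of score SDs and correlations, labelled as assumptions, as in the sensitivity table above.
5. Optionally, calculate the pooled SD and the baseline to week 12 correlation, blinded to arm, when 60 participants have completed the post-intervention assessment, and restate the detectable difference. The Monitoring section already schedules a safety review at that point.

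The cost is revised sample size text and a little more analysis. The stated power becomes slightly less favourable.

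### With the stated f = 0.22, 150 analysed participants give about 76% power, not 80%, so 150 and 188 do not follow from the plan's own inputs

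*Protocol article*

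**What the plan says.** The sample size rests on the primary comparison, the week 12 motor score adjusted for baseline. The Sample size section of the protocol article describes the model thus: "This power analysis is for a one-way fixed effects analysis of covariance with two levels". The planned difference and correlation are given as "Assuming the more conservative difference in mean changes in AIS Motor Score between the groups of 4.0" and "a correlation between the baseline and week 12 ASIA Motor score of 0.8". From these the plan reports that "the resulting analysis of covariance effect size (f) is 0.22".

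The next sentence ties a sample size to that f: "The corresponding total sample size of 150 participants equally distributed between experimental and control arms will yield power of 0.8". Alpha is set at 0.05, and the test is two-sided: "The analysis of variance is non-directional (i.e., two-tailed), which means that an effect in either direction will be interpreted". After an allowance of 20% for dropout, "the final sample size for this study is calculated to be 188 patients".

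No SD for the week 12 score is stated. The only SDs given are those of the pilot changes, 1.0 and 0.5.

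**The concern.** Power in this model depends only on f, N, alpha and the degrees of freedom, and the section states all of them. The claim can therefore be checked without any outside figure, and it fails: an f of 0.22 does not lead to 150 participants at 80% power.

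This is the only justification given for the size of the trial on its confirmatory endpoint. If f = 0.22 is the right figure, the chance of missing a true 4.0-point difference at the planned dropout is about 24% rather than 20%. A null result would then be read against a power that the design does not have.

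**Working it through.** **Inputs, all from the Sample size section:** two arms, 1:1; one covariate (baseline motor score); two-sided alpha 0.05; f = 0.22; N = 150 analysed; claimed power 0.80; dropout 20%; difference 4.0; correlation 0.8.

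**Step 1. The plan's dropout step.** 150 / (1 − 0.20) = 187.5, rounded up to 188. This reproduces, so any error lies before it, in the step from f to 150.

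**Step 2. Power at the stated f and N.** The test statistic is a noncentral F with 1 and N − 3 = 147 degrees of freedom.

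- Noncentrality: λ = f² × N = 0.0484 × 150 = 7.26
- Power = P(F′(1, 147; λ = 7.26) > the 95th percentile of F(1, 147)) = **0.763**
- Check by normal approximation: √7.26 = 2.694; 2.694 − 1.960 = 0.734; Φ(0.734) = 0.769

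The claimed 0.80 is not reproduced.

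**Step 3. N needed at f = 0.22.** The smallest even total with power of at least 0.80 is **166** (164 gives 0.7997). With 20% dropout, 166 / 0.80 = 207.5, so **208** randomised. The normal approximation gives 164 analysed and 205 randomised.

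**Step 4. Could rounding of f explain it?**

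| f | Power at N = 150 | N for 80% power |
|---|---|---|
| 0.215 | 0.744 | 172 |
| 0.220 | 0.763 | 166 |
| 0.225 | 0.782 | 158 |
| 0.230 | 0.799 | 152 |

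N = 150 gives exactly 0.80 at f = 0.2303, which rounds to 0.23.

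**Step 5. Could another reading explain it?**

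- Ignoring the covariate's degree of freedom: 0.763.
- Noncentrality based on residual degrees of freedom instead of N: 0.755 to 0.758.
- One-sided test: about 0.85, with N = 128 by normal approximation. The plan says two-sided.
- Treating 0.22 as unadjusted and dividing by √(1 − 0.8²) = 0.6, so f = 0.367: power 0.994, N = 62. The plan calls 0.22 the ANCOVA effect size, so the adjustment is already in it.

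None of these gives 150 at 80% power.

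**Step 6. What the gap means in points and dropout, taking f = 0.22 as correct.**

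- Two equal arms have f = difference / (2 × SD), so the adjusted SD is 4.0 / (2 × 0.22) = 9.09.
- Difference detectable at 80% power with 150 analysed: 2 × 0.2303 × 9.09 = 4.19, or about 4.2 points.
- Power if all 188 are analysed: 0.851.
- Highest dropout that keeps 80% power: (188 − 166) / 188 = 11.7%, or about 12%.

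**The case against.** The strongest reply is that f, N and power disagree, but the document does not show which one is wrong. At f of about 0.23, N = 150 and power 0.80 agree. If f was in fact 0.2299 and was cut off to 0.22 instead of rounded, power is 0.799 and only the printed f is at fault. With a 4.0-point difference and r = 0.8, that f corresponds to a raw SD of about 14.5 (2 / (0.2299 × 0.6)), against about 15.2 for f = 0.22 (2 / (0.22 × 0.6)). Both SDs are back-calculated; neither is in the plan. This point stands: the 24% type II error and the 4.2 points are conditional on f = 0.22. It does not remove the contradiction, because on that account the printed f is wrong and still needs correcting.

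Second, 188 does follow correctly from 150. That is right. It fails to follow from f = 0.22 only because it inherits the 150.

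Third, the gap is small, changes nothing in conduct or analysis, and closes if dropout stays at or below about 12%. This is a fair statement of its size. But the plan's own planning case is 20% dropout. The planned multiple imputation keeps all 188 in the analysis set, yet it does not in general restore the information lost with missing week 12 scores, so 150 remains the basis on which the power should be judged.

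**Conclusion.** The concern holds. The power statement for the primary endpoint is inconsistent with the effect size printed in the sentence before it. At f = 0.22, two-sided 0.05 and 150 analysed, power is 0.763 against the stated 0.80, and 166 analysed (208 randomised) would be needed against 150 and 188. The shortfall is 3.7 percentage points, or about 10% of the analysed sample required (16 of 166).

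The contradiction rests only on figures in the document. The direction of the error does not: it assumes that f = 0.22 is the intended value. Without an SD for the week 12 score this cannot be settled from the document, and the pilot change SDs of 1.0 and 0.5 do not lead to 0.22.

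**What to change.** Keep 188 and correct the power sentence. If f = 0.22 is the intended value, it could read:

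> *With 150 analysed participants the trial has 76% power for f = 0.22 (a difference of 4.0 points), or 80% power for a difference of about 4.2 points. Power of 80% at 4.0 points needs about 166 analysed, that is, dropout of no more than about 12%.*

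If 0.22 is itself the misprint, correct f to the value actually used (about 0.23 would be consistent with 150 and 80%). In either case, state the assumed SD of the week 12 score and the unrounded f, so that a reader can reproduce the step from the 4.0-point difference to f and from f to N.

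The cost is one corrected sentence and, in the first case, a slightly less favourable stated power. No participants are added, and the design and analysis are unchanged.
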